### Sampling and data collection

As a substudy within the ADAPT-Sepsis trial, all RISC-sepsis procedures and sampling will occur within the trial. Sampling will occur during the ADAPT-Sepsis intervention period when blood is sampled daily. While additional blood samples are taken from patients for RISC-sepsis, there is no increase in number of sampling episodes. Patients will have blood sampled on alternate days up to four sampling points (days 1, 3, 5 and 7). Blood for flow cytometric analysis will be collected in Cyto-Chex (Streck, La Vista, USA) blood preservation tubes before shipping to a central testing hub (Newcastle University). Serum will be collected, frozen and stored at site until the end of the recruitment period.

Baseline clinical data and outcome data will be obtained from the ADAPT-sepsis data collection. Baseline data will include admission diagnosis, site of infection, acute physiology and chronic health evaluation (APACHE) II and sequential organ failure assessment scores and sepsis bundle care elements in the first 24 hours. In addition, at each RISC-sepsis sampling point, the circulating white cell count and differential count will be recorded.

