### Sample size

The sample size is based on detection of a difference in antibiotic durations between the ‘sepsis-associated immunosuppression’ and ‘non-immunosuppressed’ groups. The 2016 Surviving Sepsis Campaign guidelines recommended 7–10 days of antibiotics for patients with sepsis.^27^ We have assumed that patients with sepsis-associated immunosuppression will have longer durations (10 days) and so with a SD of 6 days (derived from the ADAPT-sepsis trial), then a sample of 180 patients is required to detect a difference of 3 days in antibiotic treatment between the ‘sepsis-associated immunosuppressed’ and ‘non-immunosuppressed’ patients with 90% power, a 5% alpha and a 5% withdrawal rate.

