### Data analysis plan

A formal analysis plan will be finalised and deposited on an open access platform before the database is locked.

For the primary objective, the time it takes for antibiotics to be stopped in patients during the ADAPT-sepsis biomarker-guided antibiotic phase will be summarised and the distribution of the outcome described for the ‘sepsis-associated immunosuppression’ and the ‘non-immunosuppressed’ groups. The mean number of antibiotic days will be compared between groups obtained from linear regression models and adjusted for confounding variables. In addition, each of the cellular markers will be assessed as a continuous outcome. The change in cellular markers between each time point will be correlated with the number of days on antibiotics using Spearman’s correlation coefficient. One sample t tests will be used to assess the changes between time points.

The trial outcomes of 28-day antibiotics, hospital-acquired infections and length of ICU-stay and hospital-stay will be summarised for the ‘sepsis-associated immunosuppressed’ and ‘non-immunosuppressed’ groups. Differences between groups will be assessed using linear regression for continuous variables and logistic regression for categorical variables. We will describe the difference between the groups using p values, point estimates and 95% CIs.

For the secondary objective, we will assess the difference in the PCT/CRP levels and cellular markers for patients who met the criteria for ‘sepsis-associated immunosuppressed’ and when immune profile recovered (ie, became ‘non-immunosuppressed’). Assessments will be captured over time, and we will compute a longitudinal analysis (taking time as a random effect) to assess the difference in the two groups.

Subgroup analyses:

Exploratory analysis will be carried out for the following subgroups:

Patients receiving critical care for a medical versus a surgical cause of sepsis;Patients receiving critical care because of trauma versus non-trauma;Patients receiving critical care because of a community-acquired infection versus a hospital-acquired infection;Infection site: community-acquired pneumonia; hospital-acquired pneumonia; urinary tract infection; intra-abdominal infection or positive blood culture;Patients with septic shock, as defined by persistent hypotension requiring vasopressors to maintain an mean arterial pressure (MAP) ≥65 mm Hg and a serum lactate of >2 mmol/L.^1^

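### As written, the longitudinal model for the secondary objective makes time the random effect and names no patient-level term, so it does not account for repeated samples from the same patient

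*Protocol article*

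**What the plan says.** The Data analysis plan of the protocol article states for the secondary objective: "we will compute a longitudinal analysis (taking time as a random effect) to assess the difference in the two groups". The outcomes are PCT, CRP and the cellular markers. The comparison concerns patients who met the immunosuppression criteria and the point "when immune profile recovered (ie, became" non-immunosuppressed, so one patient may contribute samples in both states.

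On repeated measurement, Sampling and data collection says: "Patients will have blood sampled on alternate days up to four sampling points (days 1, 3, 5 and 7").

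Beyond "taking time as a random effect", the article gives no other element of this model: no patient random effect, no within-patient covariance and no clustering. It does say that further detail is to come: "A formal analysis plan will be finalised and deposited on an open access platform before the database is locked". That plan is not shown.

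**The concern.** Samples from one patient resemble each other more than samples from different patients, and a longitudinal model has to carry that correlation. A random effect for time does not. It absorbs shifts on a given day that are common to everyone and leaves the likeness within a patient in the residual. Nor is time a natural random factor here, since the days are four chosen levels and not a sample of possible times.

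Two things are at stake. If the groups are different patients, the standard error is too small and false positives rise. If the contrast is suppressed versus recovered in the same patient, the pairing is not used and precision is lost. The Rationale section gives weight to whether CRP and PCT fall while cellular defects resolve, and this is the model meant to speak to that.

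**Working it through.** **The plan's own figure.** The article gives no figure for the longitudinal model. Its sample size reproduces: a difference of 3 days, SD 6, two-sided 5% and 90% power need 85 per group, 170 in total; 170 / 0.95 = 179, against 180 stated. None of this uses the longitudinal model. It supplies the number of patients below: 180 × 0.95 = 171.

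**Inputs.** 171 patients; up to four samples each (Sampling and data collection); marker variance set to 1; within-patient correlation ρ, which is not in the documents and is assumed to be 0.3, 0.6 or 0.8, equal between all days.

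**Contrast between patients, four samples each.** Split 85 and 86, the model without a patient term reports SE = √(1/340 + 1/344) = 0.0765. The true SE is larger by √(1 + 3ρ). The actual error is 2 × [1 − Φ(1.96 / √(1 + 3ρ))].

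| ρ | 1 + 3ρ | true SE / model SE | true SE | actual error at nominal 5% |
|---|---|---|---|---|
| 0.3 | 1.9 | 1.38 | 0.105 | 15.5% |
| 0.6 | 2.8 | 1.67 | 0.128 | 24.1% |
| 0.8 | 3.4 | 1.84 | 0.141 | 28.8% |

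With two samples per patient the factor is √(1 + ρ), and over ρ = 0.2 to 0.8 the error is 7% to 14%. With a patient random intercept, the model SE equals the true SE.

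**Contrast within patients.** Assume that every patient starts suppressed and that one third (57) recover after sample 1, one third after sample 2 and one third after sample 3. Remove day means from the group indicator. Only days 3 and 5 still carry information:

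- switch after sample 1: −2/3, −1/3 (sum −1, sum of squares 5/9)
- switch after sample 2: 1/3, −1/3 (sum 0, sum of squares 2/9)
- switch after sample 3: 1/3, 2/3 (sum 1, sum of squares 5/9)

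The total sum of squares is 57 × 12/9 = 76, so the model SE is 1/√76 = 0.115. The squared patient sums total 57 × 2 = 114. Hence (true SE / model SE)² = (1 − ρ) + ρ × 114/76 = 1 + 0.5ρ. With a patient effect, the information is [76 − 114ρ/(1 + 3ρ)] / (1 − ρ), and the SE is one over its square root.

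| ρ | true SE / model SE | actual error | true SE | SE with a patient effect | ratio of the last two |
|---|---|---|---|---|---|
| 0.3 | 1.07 | 6.8% | 0.123 | 0.110 | 1.1 |
| 0.6 | 1.14 | 8.6% | 0.131 | 0.088 | 1.5 |
| 0.8 | 1.18 | 9.8% | 0.136 | 0.064 | 2.1 |

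These figures take day as fixed. With day as a random effect of small variance (0.05), the understatement is 1.06 to 1.14 at ρ = 0.3 to 0.7.

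**Dependence on switch times.** If half switch after sample 2 and half after sample 3, only day 5 carries the contrast. The model SE is then right (ratio 1.00), but it is 1.1, 1.4 or 1.96 times that of a model with a patient effect. If all switch after sample 2, group and day coincide and, with day fixed, the contrast cannot be estimated.

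**The case against.** The strongest reply is that a longitudinal analysis normally links measurements within a patient, so the parenthesis may be shorthand for a time coefficient that varies by patient. That would model some of the correlation. It stands as a possible reading, but it does not rescue the sentence. With a patient-specific slope and no patient intercept, four samples each and equal within-patient correlation, the error for a between-patient contrast is still about 10% to 27% over ρ = 0.3 to 0.8, depending on how the days are coded.

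A second reply is that covariance detail belongs to the analysis plan still to come. Silence would indeed be no finding. Here the article commits to a structure, and a later plan must either inherit it or depart from it.

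A third is that the large error rates need a between-patient contrast and near-complete sampling. That stands. The sentence mentions two groups, but what precedes it reads largely as a within-patient comparison, for which the error is modest. The definition of immunosuppression also requires abnormalities to persist for 3 or more days, which leaves less room for a switch after sample 1. Under later switch times the cost is mainly precision.

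Three stronger readings are tempting and are not supported:

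- That the study treats samples as independent. The article never says so; it follows only if the stated model is fitted literally.
- That promised p values and 95% CIs are invalid. They are promised in the paragraph on trial outcomes (28-day antibiotics, hospital-acquired infection, length of stay), which does not use this model.
- That within-patient standard errors are overstated by 1/√(1 − ρ), that is 1.2 to 2.2 times. That formula leaves out the day effect that the model contains. With day effects and evenly spread switch times, the model SE is slightly too small.

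**Conclusion.** The point holds as a rule that is wrong as written: the random effect is attached to the planned days, and the unit that is actually repeated has no term. The consequence depends on the contrast. Between patients with four samples each, the error is about 16%, 24% or 29% in place of 5%. Within patients with evenly spread recovery, it is about 7% to 10%, and the true standard error is 1.1, 1.5 or 2.1 times what a patient effect would give.

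These sizes rest on an assumed equal correlation of 0.3, 0.6 or 0.8, on complete sampling of 171 patients and, for the second contrast, on the assumed switch times. The documents fix none of these. The point is confined to the secondary objective of a study that calls itself exploratory. The 180 patients and the regression of antibiotic days do not depend on it.

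**What to change.** Replace the parenthesis about time with: *a linear mixed model with a random intercept for patient (and a patient-specific slope over days if the data support it), or an equivalent within-patient covariance structure, and sampling day as a fixed effect.* State that the patient term serves both the between-group contrast and the suppressed-versus-recovered contrast within patients, and carry the same wording into the analysis plan before database lock. If the authors already intend this, it is a clarification.

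The cost is one line, with no change to recruitment, sampling or data collection. Between-patient confidence intervals become wider than the literal model would report, by 1.38, 1.67 or 1.84 times with four samples each at the assumed correlations. That width is the correct one. Within patients, precision improves.

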### Study duration

The study was planned to commence in April 2020, but due to the COVID-19 pandemic, the start date was delayed until August 2020. Further delays were experienced during the optimisation of flow cytometry and site set up phases. Recruitment commenced in May 2022 and is ongoing. The study is planned to complete in April 2023.

### Public and patient involvement

Members of the public and patients were involved through the Pathfinder group, a group of critical survivors and representatives in the North East of England. The Pathfinder group was involved in developing the research question and lay summary. Ongoing public and patient involvement is through the ADAPT-Sepsis Trial Management and Trial Steering Groups, which incorporate RISC-sepsis oversight, and have members of the Intensive Care Society’s Patient and Relatives group.

### Ethics and dissemination

As a substudy, the protocol has been incorporated into the ADAPT-sepsis protocol and ethical approval has been granted by the South Central—Oxford C Research Ethics Committee (IRAS 209815). The study has been registered with the ISRCTN registry (86837685) and adopted by the UK NIHR Clinical Research Portfolio. The study is managed by the Warwick Clinical Trials Unit and Sponsored by The University of Manchester. Independent study oversight is provided by the ADAPT-Sepsis trial steering committee.

The study will be reported in line with the Strengthening the Reporting of Observational Studies in Epidemiology guidelines for observational studies.^28^ Findings will be disseminated by peer-reviewed publications and at national and international meetings. In addition, findings will be disseminated via public and patient groups and through social media.
